# research design and methods

## Overview

1. Study Setting: Umlazi/Philasande Research Clinic and Gateway Umlazi Clinic
2. Study Design: This study is a prospective two-arm, quasi-experimental design comparing a primary health care intervention plan with usual care.
3. Target Population: HIV infected women attending PHC
4. Study population: HIV infected women aged from 18 to 49 years of age and receiving HIV care at PHC clinics.
5. Inclusion criteria

- HIV infected women
- On ART for at least 1 year
- Equal to/older than 18 years of age
- Equal to/younger than 49 years of age
- Plans to remain in the study catchment area for at least 3 years

1. Exclusion criteria

- Participant declines study participation

1. Sampling

• Size of sample

400 HIV-infected women consisting of an intervention arm of 200 women co-enrolled in the PROMOTE study at the Umlazi CRS (see method of sampling for details), and a control arm of 200 women receiving HIV care at the PHC. With a 20-30% estimated prevalence of metabolic syndrome in people living with HIV without any specific intervention in the risk factor modification of cardiovascular disease and a proposed 10-15% estimated incidence of metabolic syndrome in the intervention arm, 132 participants per arm would allow for 80% power. An additional 10% can be added to allow for loss to follow-up. The larger proposed sample size will allow for external validity / generalizability.

- Method of selecting sample

Two HIV-infected female cohorts will be matched for receipt of ART duration >1 year and for age will be compared in the study. Method of selection will be via convenience sampling.

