**Intervention group**: There are 245 HIV infected women between 18 and 49 years of age, who have been on ART for more than 1 year and attending the CAPRISA Research Clinic in Umlazi. These women were enrolled into the PEPFAR PROMise Ongoing Treatment Evaluation (PROMOTE) observational study from May-June 2017. This study has been implemented to provide long-term follow-up data on safety outcomes of widespread use of combination antiretrovirals (cART) among an already well-characterized cohort of HIV infected mothers and their children who previously enrolled in the multi-site PROMISE study. This cohort was selected for the proposed intervention arm because the principal investigator is based at the research clinic. Women will be briefed at their next PROMOTE study visit and the 1^st^ 200 interested candidates meeting all eligibility criteria will be co-enrolled into the Intervention arm of the Sub-study.

**Control group**: The Tier data base will be used to select HIV infected women aged between 18-49 years, receiving ART for more than 1 year at the Umlazi Gateway PHC. Scheduled clinic visits at similar time points to the anticipated clinic visits in the intervention group will be used to establish a list of potentially eligible women. Following a matched pool of data, the first 200 women fulfilling the inclusion criteria, who attend the clinic for their next appointment and who consent to study participation will be enrolled.

1. Data sources

- Intervention group: Each participant in the intervention group will be assigned a new Participant identifier number (PID) in addition to the PROMOTE PID. History taking and physical exam, as well as laboratory results and where applicable ultrasound reports, will be entered directly into a data collection tool on a Microsoft Excel spreadsheet (Appendix I).
- Control group: Participants will be assigned a PID in addition to their clinic chart number. Information from clinic patient medical records will be entered directly into the data collection tool (Appendix II). At the final study visit; history, physical exam, lab report finding and ultrasound findings (where applicable), will be source documented.

1. Measures to ensure validity

- Internal
- The prospective nature of the study, large sample size, careful matching between cohorts by age category and by duration of ART aims to counteract the potential for selection bias.

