- **Intervention group**: The prevalence of CVD risk factors will be determined by data collection through history taking, physical examination, and laboratory and radiology investigations as per the data collection tool. CVD risk assessment will be performed annually using a combination of the WHO and International Society of Hypertension cardiovascular risk prediction (WHO/ISH) and the DAD CHD equation. The intervention proposed is a modified WHO PEN algorithm incorporated into HIV management guidelines at study entry. Trends in all risk factors will be monitored, and new risk factors identified, with 6 monthly intervention during the first year, and annually for three years thereafter.
- **Control group**: Following informed consent, data will be collected from the participants ARV clinic medical chart as per the data collection tool. Standard of care HIV management and primary health care will be provided by public sector clinic staff according to current national guidelines. No study investigations or study questionnaires will be carried out at entry visit until the final study visit. There will be regular telephonic follow up with the participants to maintain study retention. Chart review data collection at 6 monthly intervals. CVD risk factors, as per outcomes described above, will be measured by the study at a single 3 year final study visit. Information obtained will be conveyed to the clinic staff for further management if required.

1. Plan for Data handling/processing

- Data will be analysed using SAS or SPSS software

1. Statistical methods

- Descriptive statistics-continuous variables will be represented by means, medians, prevalence, standard deviation.

The categorical variables will be represented by N+%

- Analytic statistics

The continuous variables will be compared by use of t-tests or Wilcoxon rank sum tests.

The categorical variables will be compared using Chi sq or Fisher’s exact test/

- Logistic regression will be applied to identify predictors of cardiovascular disease between the two arms, and between those participants who exhibit atherosclerosis by carotid intima thickness and those who don’t.

1. List of possible confounders

- Women in the intervention group are already enrolled in a study with controlled settings. These women may have commenced ART with a higher baseline CD4 counts.
- Multivariate logression analyses will be utilized in order to control for confounders.

1. List of associations to be measured

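### The ART-duration match is defined as the entry criterion and so balances nothing as written, and CD4 at ART start, a confounder the plan names, is not in its variable list

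*Protocol*

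**What the plan says.** All locations are in the Protocol, section Overview.

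- **Inclusion criteria:** "On ART for at least 1 year", for both arms.
- **Method of selecting sample:** "Two HIV-infected female cohorts will be matched for receipt of ART duration >1 year and for age". Selection is by convenience sampling.
- **Source pools:** the intervention pool is 245 women "who have been on ART for more than 1 year and attending the CAPRISA Research Clinic in Umlazi", of whom the first 200 interested and eligible are enrolled. Controls are drawn from women "receiving ART for more than 1 year at the Umlazi Gateway PHC".
- **Control enrolment:** "Following a matched pool of data, the first 200 women fulfilling the inclusion criteria, who attend the clinic for their next appointment" and who consent are taken.
- **Measures to ensure validity, Internal:** "careful matching between cohorts by age category and by duration of ART aims to counteract the potential for selection bias".
- **List of possible confounders:** intervention women are already in a study with controlled settings, and "These women may have commenced ART with a higher baseline CD4 counts". Multivariable regression is to control for confounders.
- **List of variables:** age in 5-year categories, ART duration in years and CD4 count appear for both arms. No row gives CD4 at ART start. The table of associations has a single CD4 row.

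**The concern.** Matching is one of the main protections this quasi-experimental comparison claims. If the duration match is only the entry threshold, the arms can differ widely in years of treatment and still be called matched. The protocol's literature review links ART to lipid changes and insulin resistance, and its table of associations relates age, ART duration and CD4 to every risk factor listed as an outcome.

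The arms also differ in origin. Intervention women are mothers from an earlier multi-site study, and controls are ordinary clinic attenders. The protocol itself suspects a CD4 difference at ART start, but the variable that would let the analysis address it is not listed.

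There is little to fall back on. Controls have no study investigations until the final visit, and the chart-review column for controls has no waist circumference or fasting glucose. A comparison adjusted for metabolic syndrome at entry is therefore not available from the listed data, which leaves matching and covariate adjustment to carry the between-arm inference.

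**Working it through.** The protocol gives no figure for this point, so most of the check sets its statements side by side.

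**1. What the duration match does.** Entry requires at least 1 year of ART. Both source pools are filtered at more than 1 year. The match is on more than 1 year. The entry rule and the match differ only for a woman at exactly 1 year. An arm averaging 2 years and an arm averaging 8 years would both satisfy it. No band, caliper or ratio is given anywhere, so the only definition of the duration match in the document is in effect the eligibility filter.

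**2. Whether the validity section repairs this.** It speaks of matching by age category and by duration of ART, which may mean something finer. It does not say what, and it sits beside the definition in step 1 without replacing it.

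**3. Whether balance survives enrolment.** The control pool is described as matched, but enrolment from it goes to the first 200 eligible attenders who consent. In the intervention arm it goes to the first 200 of 245 who are interested (200/245 = 82%). No quota carries the pool's balance through to the women enrolled.

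**4. Whether the named confounder can be adjusted for.** The confounder is CD4 at ART start. The listed variable is CD4 at study or chart-review time points, when every woman has had at least a year of treatment. A later, on-treatment value is a different variable.

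**5. What can be adjusted for.** Age category and ART duration in years are listed for both arms at every stage, so imbalance in these can enter the planned regression.

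**6. Size.** The document gives no distribution of ART duration or of CD4 at ART start in either arm, and no slope of metabolic syndrome on either. Its one related trend, obesity rising from 34.4% to 47% over 3 years, or (47 − 34.4)/3 = 4.2 points a year, concerns obesity after HIV acquisition and cannot be converted.

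The CD4 question can be illustrated only under assumed values: no intervention effect, a control rate of 25%, 200 women per arm, and low CD4 at ART start carrying a risk ratio RR, with prevalence q_I in the intervention arm and q_C in the control arm. The intervention rate is then 25% × [1 + q_I(RR − 1)] / [1 + q_C(RR − 1)].

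- RR 1.25, q_I 30%, q_C 50%: 25% × 1.075/1.125 = 23.9%, a spurious difference of 1.1 points.
- RR 2.0, q_I 20%, q_C 60%: 25% × 1.2/1.6 = 18.75%, a spurious difference of 6.25 points.

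With a two-sided 5% test, also assumed, the chance of a significant result favouring the intervention is about 4% in the first case and 33% in the second, against a nominal 2.5%. For scale, the planned rates are 20-30% and 10-15%, a difference of 10 points at the lower ends and 15 at the upper ends. These inputs are not in the document, so the range shows a mechanism and is not an estimate.

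**The case against.** The strongest reply has four parts.

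*The sampling sentence is loose shorthand.* The validity section refers to duration of ART, and controls follow from a matched pool, so finer matching may be intended. This stands as far as intent goes. A reader might infer that no duration matching will take place, and the document does not establish that. What it shows is that the one definition given is empty and that the two statements need reconciling.

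*The planned regression handles imbalance.* For age and ART duration this largely stands. A reader might infer that imbalance in them passes undiminished into the arm difference. It need not, because both are recorded in both arms. Adjustment works less well where the arms barely overlap, and banded selection prevents that. The reply does not reach CD4 at ART start.

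*CD4 at ART start may be captured anyway.* The data collection tools are appendices whose content is not visible, control data come from charts, and the intervention cohort is described as well characterised. A reader might infer that the value will not be collected, and that cannot be shown. The supportable statement is that the variable list omits it.

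*Its importance is unproven.* The plan says only that the women may have started at higher counts. The literature review cites a local, mainly female study in which carotid thickening was associated with traditional rather than HIV-specific factors. This limits how much weight the point can bear. Still, the protocol chose to name this confounder and promised to adjust for it.

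The covariate set and the scale on which age is modelled can be left to an analysis plan. The selection rule and the data to be collected have to be fixed before enrolment.

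**Conclusion.** The point holds in limited form. As written, the ART-duration match repeats the entry criterion and cannot do what the validity section asks of it. CD4 at ART start is named as a possible confounder but is absent from the variable list, so the promised adjustment cannot be made from the variables listed. It is not the only confounder named: co-enrolment in a controlled study is listed too. That one coincides with arm and cannot be separated by regression, so CD4 at ART start is the only named one that is a patient-level covariate.

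A reader might want a figure in percentage points for the bias. The documents do not support one, since neither the gap between arms nor its effect on metabolic syndrome is given. The 1 to 6 point illustration for CD4 rests wholly on assumed values, and no figure is offered for ART duration, which the regression can partly address. The case for change is that the remedy is cheap and the comparison is non-randomised with no study-measured baseline in the control arm.

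**What to change.** 1. Reconcile the sampling and validity sections by stating the matching rule. Select controls within cells of age category by ART-duration band (for example 1 to under 3, 3 to under 6, and 6 or more years), set to the intervention arm's distribution, using ART start dates from existing records.
2. Apply the cells as quotas at enrolment, so that the balance holds among the women who consent and not only in the listed pool.
3. Add CD4 at ART start to the variable list for both arms, taken from existing records, and report its completeness by arm. If the data collection tools already hold it, say so in the list.
4. Adjust the between-arm comparison for CD4 at ART start together with age and ART duration, which are already collected.

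The cost is revised selection wording and one chart item. Control recruitment will be slightly slower as cells fill, and some CD4 values at ART start will be missing.

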# BACKGROUND

Worldwide, there are 36.7 million people living with HIV (PLWH) with a marked increase in uptake of antiretroviral therapy (ART) and a steep decline in numbers of AIDS-related deaths. However globally the leading cause of death is from cardiovascular disease (CVD) with the majority of deaths occurring in developing countries. The path to atherosclerotic CVD progression, mainly coronary artery and cerebrovascular disease, remains silent until advanced stages and the end result is significant disability or death.

An estimated 16.6% of South Africans aged between 15-49 years are living with HIV, of which 23.2% are women of reproductive age. A reduction in HIV-related mortality among women of reproductive age in South Africa is largely attributed to increased access to antiretroviral treatment resulting in non-communicable diseases such as diabetes, cerebrovascular disease and hypertension surpassing HIV as the leading causes of death. Although there appears to be higher risk of CVD in HIV infected men, international studies have shown that the risk of CVD in HIV infected women is significant. As more HIV infected South African women of reproductive age access antiretroviral treatment resulting in potential increased life expectancy, there remains a paucity of data for non-communicable co-morbidities in this vulnerable population group.

In addition to the well-recognized traditional risk factors for CVD in HIV uninfected women, there is increasing evidence of HIV-related chronic inflammation and immune activation and certain antiretroviral drugs that contribute to the increased presence of metabolic syndrome in PLWH. The presence of metabolic syndrome defined by elevated blood pressure, glucose, dyslipidaemia and abdominal obesity, doubles the risk of cardiovascular disease. A systematic review has shown that the mean prevalence of metabolic syndrome among PLWH in Africa was 30.5%. Local studies have demonstrated an increase in obesity in the first 3 years after HIV acquisition and that obesity is more pronounced in black females compared to males. Investigators have further demonstrated that South Africa is facing an epidemic of hypertension, and that there is a high prevalence of concurrent hypertension and HIV highlighting the need for improved integration of management guidelines. The Heart of Soweto study has shed light on the rising incidence of acute coronary syndrome and other cardiovascular diseases in Black South Africans.

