# LITERATURE REVIEW

## Introduction:

A Sciencedirect and Pubmed literature search of multi-national clinical trials, observational studies and systematic reviews all allude to the increasing incidence of cardiovascular disease (CVD) in HIV uninfected and infected populations in developed and developing nations, and in young and old([2-7](#_ENREF_2)). Traditional risk factors for CVD, namely genetic predisposition and behavioural risk factors such as the use of tobacco, excessive alcohol consumption, sedentary lifestyle, and inappropriate diet are well known in the general population, and are becoming more evident in people living with HIV (PLWH) in low and middle income countries (LMIC) due to poverty and emerging factors such as increased urbanization([8](#_ENREF_8)).

In African regions and other low and middle-income countries the increased access to antiretroviral treatment and treatment success is unfortunately accompanied by a rise in cardio-metabolic disease ([3](#_ENREF_3), [4](#_ENREF_4), [9](#_ENREF_9)). In addition to known traditional risk factors, HIV through direct mechanisms of persistent immune activation and chronic inflammation in an ageing treated HIV-infected population, and indirectly through the effects of antiretroviral treatment (ART), contribute to the increased presence of intermediate risk factors of CVD in PLWH ([5](#_ENREF_5), [10](#_ENREF_10)). The intermediate risk factors, namely elevated blood pressure and blood glucose, dyslipidaemia and abdominal obesity, make up an entity called metabolic syndrome and the presence of this syndrome doubles the risk of CVD. A systematic review has shown that the mean prevalence of metabolic syndrome among PLWH in developing countries was 30.5%, 21.5%, and 21.4% in Africa, Asia, and South America, respectively. The most common metabolic abnormality across all countries in this review was the presence of a low high-density lipoprotein ([6](#_ENREF_6)).

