The WHO PEN assesses CVD risk by means of the WHO and International Society of Hypertension (WHO/ISH) cardiovascular risk prediction charts specific to 14 epidemiological sub-regions ([43](#_ENREF_43), [44](#_ENREF_44)). These guidelines have been developed in order to identify people who are at a 10 year risk of developing a major cardiovascular event based on age, gender, systolic blood pressure, presence of diabetes mellitus, total blood cholesterol and tobacco use. Risk assessment begins at age of 40. CVD risk may be higher than indicated by the charts in persons already on antihypertensive therapy, who are obese and who have a sedentary lifestyle. Family history of premature CHD or stroke, elevated triglycerides, low HDL, elevated C-reactive protein, presence of microalbuminuria, tachycardia, fasting glycaemia or impaired glucose tolerance, and socioeconomic deprivation may also indicate a higher risk. Being specific to sub-regions, the WHO/ISH cardiovascular risk is a more suitable CVD risk assessment tool in our setting. Studies assessing the WHO PEN intervention in the general population have shown that it is a feasible management plan in reducing cardiovascular risk([45](#_ENREF_45)). However HIV risk is not factored in and the age of risk assessment should ideally begin at a younger age.

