- Information bias in chart review will be controlled by training of staff involved in data collection. Missing information
- Loss to follow up – a retention plan will be place to send clinic appointment reminders by sms or whatsapp, telephone calls in the case of missed visits and occasionally home visits when deemed necessary.
- Laboratory sample measurements will be performed by a certified laboratory.
- External -The larger proposed sample size will allow for external validity / generalizability.

1. List of Variables to be measured and schedule of evaluations

| CVD risk factors | Intervention Arm  (at main study PROMOTE scheduled visits)  Year 1(0+6m), Year 2(12+18m), Year 3(24+30m), Final study Visit (36m) | Control Arm | |
| --- | --- | --- | --- |
|  |  | **Year 1, 2, 3 (not including end of study visit) | Year 3 (end of study-36months) |
| Non-modifiable | Age (Categories in 5 year) | Age (Categories in 5 year) | Age (Categories in 5 year) |
|  | Race (A, I, W, C, O) | Race (A, I, W, C, O) | Race (A, I, W, C, O) |
|  | Family history of CVD in first degree relatives |  | Family history of CVD in first degree relatives |
| Modifiable | Smoking (Current, Never, Past) |  | Smoking (Current, Never, Past) |
|  | Unhealthy Diet |  | Unhealthy Diet |
|  | Exercise (minutes per week) |  | Exercise (minutes per week) |
|  | ART duration in years | ART duration in years | ART duration in years |
|  | ARV regimen | ARV regimen | ARV regimen |
|  | Viral load | Viral load | Viral load |
|  | CD4 count | CD4 count | CD4 count |
|  | BMI (6monthly) | BMI (6monthly) | BMI |
|  | Waist Circumference (6 monthly) |  | Waist Circumference |
|  | Systolic BP (6monthly) | Systolic BP | Systolic BP |
|  | Pulse (6monthly) |  | Pulse |
|  | Fasting Glucose (annual) |  | Fasting Glucose |
|  | Fasting Lipogram (annual) | Fasting Lipogram | Fasting Lipogram |
|  | hsCRP (annual) |  | hsCRP |
|  | Urine Microalbumin (annual) |  | Urine Microalbumin |
|  | *Carotid intima media thickness |  | Carotid intima media thickness |
|  | CVD risk % by Framingham |  | CVD risk % by Framingham |
|  | CVD risk % by DAD |  | CVD risk % by DAD |
|  | CVD risk % by WHO/ISH |  | CVD risk % by WHO/ISH |

*Only at year 3 in women aged over 40 years **Data collection through chart review

1. Plan for Data collection

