|  | BMI | WC | Fasting lipogram | Systolic BP | Fasting  Glucose | Urine microalbumin | hsCRP | Carotid initima medial thickness |
| --- | --- | --- | --- | --- | --- | --- | --- | --- |
| Age | x | x | x | x | x | X | x | X |
| Family History  of CVD | x | x | x | x | x | X | x | X |
| Tobacco use | x | x | x | x | x | X | x | X |
| Diet | x | x | x | x | x | X | x | X |
| Exercise | x | x | x | x | x | X | x | X |
| ART regimen | x | x | x | x | x | X | x | X |
| ART duration | x | x | x | x | x | X | x | X |
| VL | x | x | x | x | x | X | x | X |
| CD4 | x | x | x | x | x | X | x | X |
| BMI |  |  | x | x | X | X | x | X |
| WC |  |  | x | x | X | X | x | X |
| Fasting Lipogram |  |  |  | x | X | X | x | X |
| Systolic BP |  |  |  |  | X | X | x | X |
| Fasting Glucose |  |  |  |  |  | X | x | X |
| U-microalbumin |  |  |  |  |  |  | x | X |
| hsCRP |  |  |  |  |  |  |  | X |
| CVD risk % by Framingham |  |  |  |  |  |  |  | X |
| CVD risk % by DAD |  |  |  |  |  |  |  | X |
| CVD risk % by WHO/ISH |  |  |  |  |  |  |  | X |

1. Calculate cardiovascular risk as per WHO –ISH, DAD and Framingham, annually in intervention group and in the control group at year 3 and compare short term outcomes (presence of subclinical atherosclerosis by means of CMIT, presence of stroke, MI, angina -ischaemic heart disease)

1. Intervention:

**DIETARY CHANGES:** All individuals encouraged to reduce daily salt intake by at least one third and, if possible, to <5 g per day, to eat at least 400 g a day of a range of fruits and vegetables as well as whole grains and pulses and to reduce total fat and saturated fat intake

**PHYSICAL ACTIVITY:** All individuals encourage to do at least 30 minutes of moderate physical activity (e.g. brisk walking) a day, through leisure time, daily tasks and work-related physical activity.

**WEIGHT CONTROL:** All individuals who are overweight or obese should be encouraged to lose weight through a combination of a reduced-energy diet and increased physical activity

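### Only systolic pressure is a listed study variable in either arm, so the listed data cannot identify women whose raised blood pressure is diastolic only, although the study is sized on metabolic syndrome

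*Protocol*

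**What the plan says.** In the protocol's Overview, under the list of variables and schedule of evaluations, blood pressure has one row, whose intervention-arm entry begins "Systolic BP (6monthly". Across the intervention visits, the control chart review and the control month-36 visit it reads "Systolic BP (6monthly) | Systolic BP | Systolic BP". The table of associations to be measured does the same: its column headings include "Fasting lipogram | Systolic BP" and no other pressure variable. The word diastolic appears nowhere in the readable text. The schedule has no row for diagnosed hypertension or antihypertensive treatment.

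The outcome side is worded more widely. The Background refers to "The presence of metabolic syndrome defined by elevated blood pressure, glucose, dyslipidaemia and abdominal obesity", and the Introduction to the literature review says "The intermediate risk factors, namely elevated blood pressure and blood glucose, dyslipidaemia and abdominal obesity, make up an entity called metabolic syndrome". Neither limits blood pressure to systolic, and neither gives a cut-off. The sample size is argued from a "20-30% estimated prevalence of metabolic syndrome in people living with HIV" against 10-15% in the intervention arm, giving 132 per arm for 80% power; 200 per arm are planned. The first primary objective is to identify and modify cardiovascular risk factors, and the section on HIV and hypertension treats hypertension as one of them.

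For the WHO/ISH chart, systolic pressure is the stated input: the chart is "based on age, gender, systolic blood pressure, presence of diabetes mellitus, total blood cholesterol and tobacco use".

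**The concern.** Elevated blood pressure is normally established from either component. With only the systolic value listed, a woman with normal systolic and raised diastolic pressure has nothing in the listed data to show it, and no hypertension or treatment row would catch her another way.

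Three things are at stake. Measured prevalence of raised pressure would be too low in both arms. Some metabolic-syndrome cases that turn on blood pressure could be missed, which costs power on the outcome used for sizing. A fall in diastolic pressure under the intervention would leave no trace, although modifying risk factors is a primary aim. The risk chart does not fill the gap: the protocol says its use begins at age 40, while women are enrolled from 18 to 49.

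This is not a detail to leave to an analysis plan. Such a plan can set a cut-off, but it cannot recover a reading that was never collected.

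**Working it through.** **1. The plan's own figure.** The protocol states no alpha, so two-sided 0.05 is assumed. With p̄ = (p1 + p2)/2,

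n = [1.96·√(2p̄(1−p̄)) + 0.8416·√(p1(1−p1) + p2(1−p2))]² / (p1 − p2)².

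For 30% vs 15%: (1.96 × 0.5906 + 0.8416 × 0.5809)² / 0.15² = 2.711 / 0.0225 = 120.5, so 121 per arm, or 134 with continuity correction. For 28% vs 14% without correction, n = 132. The stated 132 is therefore consistent with assumptions at the upper end of the stated ranges. By contrast, 20% vs 10% needs 199 per arm.

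**2. Share of raised-pressure cases that systolic alone misses.** The documents give no distribution and no cut-off, so everything here is assumed: bivariate normal pressures, SD 15 (systolic) and 10 (diastolic), correlation ρ of 0.60 or 0.75. Two illustrative cut-off pairs are used, and neither is proposed as the right one. With a = (systolic cut-off − mean)/15 and b = (diastolic cut-off − mean)/10:

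- P(systolic raised) = 1 − Φ(a)
- P(either raised) = 1 − Φ₂(a, b; ρ)
- missed share = [P(either) − P(systolic)] / P(either)

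Low end at 130/85: mean 125/75, ρ = 0.75, so a = 0.333 and b = 1.000. P(systolic) = 0.3694 and P(either) = 0.3909, so the missed share is 0.0215/0.3909 = 5.5%.

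High end at 130/85: mean 118/80, ρ = 0.60, so a = 0.8 and b = 0.5. P(systolic) = 0.2119 and P(either) = 0.3838, so the missed share is 0.1719/0.3838 = 45%.

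| Assumed mean (mmHg) | Missed share at 130/85 | Missed share at 140/90 |
| --- | --- | --- |
| 115/74 | 25-31% | 40-45% |
| 118/77 | 28-33% | 44-48% |
| 122/80 | 26-31% | 43-47% |
| 122/74 | 8-12% | 14-19% |
| 125/75 | 5.5-10% | 10-15% |
| 118/80 | 41-45% | 60-62% |

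The range within each cell comes from ρ. Multiplying P(either) − P(systolic) by 200 gives about 4 to 34 women per arm at 130/85 and about 4 to 24 at 140/90. The first three pairs place both means about equally far, in SD units, from their cut-offs and so give a deceptively narrow band. The last three show how strongly the answer depends on that pairing.

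**3. What this could do to the sizing outcome.** The shares above are of women with raised pressure, not of metabolic-syndrome cases. The documents do not allow the second quantity to be computed. As an illustration, let a share m of metabolic-syndrome cases be missed equally in both arms with no false positives, so that p1 and p2 become p1(1−m) and p2(1−m). With N women per arm,

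power = Φ{[(p1−p2)√N − 1.96√(2p̄(1−p̄))] / √(p1(1−p1) + p2(1−p2))}.

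| m (assumed) | 30% vs 15%: risk difference | Power, 132 per arm | Power, 200 per arm | 20% vs 10%: power, 200 per arm |
| --- | --- | --- | --- | --- |
| 0 | 15.0 points | 83.5% | 95.1% | 80.2% |
| 5% | 14.25 points | 81.0% | 93.8% | 77.8% |
| 10% | 13.5 points | 78.2% | 92.2% | 75.2% |
| 15% | 12.75 points | 75.3% | 90.3% | 72.4% |

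The risk ratio stays at 2.0 in every row, because the factor (1−m) cancels.

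**The case against.** The strongest reply is that the readable protocol may understate what is collected. Data are entered through the two appended data collection tools, which are not visible here and may hold a diastolic field. History and physical examination are recorded, and the section on current risk modification speaks of blood pressure in routine clinic care without restricting it to systolic. The schedule row may be shorthand, since systolic pressure is the WHO/ISH input. This stands as a limit on confidence. It does not remove the point: diastolic pressure is still not a listed study variable, and nothing in the text requires that it be extracted or used. If the tools do hold it, the schedule should be brought into line with them.

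A reader might infer that these women are counted as free of hypertension and of the blood-pressure part of metabolic syndrome. The documents do not say so. They give no cut-off, no rule for classing raised pressure, and no statement that systolic pressure alone decides. What is supported is narrower: the listed variables cannot identify these women.

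A reader might also infer that the comparison is biased towards one arm, or that every effect measure is diluted. The same variable is listed in both arms, so nothing points to one arm. An equal loss of sensitivity shrinks the risk difference and power but leaves the risk ratio unchanged. Nor do the documents say how common diastolic-only elevation is in women of this age, so no claim about its frequency is made here.

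Finally, the loss may be modest. In the illustration at 200 per arm, power for 30% vs 15% stays at 90% or above, and the WHO/ISH score is untouched.

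**Conclusion.** The point holds as a gap between what is scheduled and what the outcome needs. Systolic pressure alone is listed in both arms, while the sizing outcome and the first primary objective rest on elevated blood pressure in general. Women with diastolic-only elevation cannot be identified from the listed variables, and a diastolic response cannot be seen.

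The size is uncertain. Under the six assumed mean pairs, the missed share of raised-pressure cases is about 5.5-45% at 130/85 and 10-62% at 140/90; other pairings could fall outside these ranges. The effect on metabolic-syndrome status should be smaller, because a missed reading matters only where pressure decides the case. That assumes not all four named components are required, and the protocol does not say how many are. If 5-15% of metabolic-syndrome cases were missed equally, power would fall by about 2 to 8 percentage points at 132 per arm (30% vs 15%), by about 1 to 5 points at 200 per arm for the same rates, and by about 2 to 8 points at 200 per arm for 20% vs 10%.

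The expectation of similar loss in both arms assumes that the intervention does not change the mix of systolic and diastolic elevation. This should be corrected but does not threaten the study. Confidence is moderate because the data collection tools are not visible.

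**What to change.** - In the schedule of evaluations, change the blood-pressure row to systolic and diastolic pressure in all three columns (intervention visits, control chart review, control month-36 visit). Make the same change in the table of associations.
- Confirm that both data collection tools have a diastolic field, and add it if not.
- State one rule for classing blood pressure as elevated for outcome purposes, met if either component is raised, with the same prespecified cut-offs in both arms. The choice of cut-offs is for the study team.
- Keep systolic pressure alone as the input to the WHO/ISH chart.

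The cost is one extra number from the same cuff reading or chart entry, with no added visit, staff or procedure. Where a control chart holds no diastolic value, record it as missing and do not treat it as normal.
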